#### **Pharmacokinetics:**

***Assessment of drug-drug interaction between VL treatment given and antiretroviral drugs.***

#### ***Amphotericin B***

Limited clinical studies have been done on the pharmacokinetics of (liposomal) amphotericin B in the treatment of visceral leishmaniasis. The pharmacokinetics of liposomal amphotericin B have been shown to be non-linear, pointing at saturation of kinetics, which makes extrapolation of previous findings done with lower doses of liposomal amphotericin B as antifungal difficult. Interactions between amphotericin B and antiretroviral drugs have not been well studied, also not in the treatment of other HIV-co-morbidities. Amphotericin B has been associated with modulation of metabolic CYP450 enzyme activity, which has been implicated most notably with changes in PI and NNRTI metabolism and thus HAART exposure. Some data suggest that this effect is less significant for the liposomal formulation, although good studies are absent for liposomal amphotericin B. Little is known about the exact pharmacokinetics of high-dose liposomal amphotericin B, although it tends to accumulate in the liver, the metabolic site of action for most PIs and NNRTIs. Also, increased rates of renal toxicity have been observed when amphotericin B is combined with tenofovir and therefore concomitant or even subsequent

administration of these compounds should be closely monitored. The combination of zidovudine and amphotericin B has been associated with additive myelosuppressive effects, particularly anemia.

For (liposomal) amphotericin B, a high variability in pharmacokinetics has previously been described between different study populations reflecting the possible influence of a variety of pathophysiological changes on its pharmacokinetics with a tendency of obviously lower levels in critically ill patients. However, nothing is known about the effect of HIV-VL morbidity on the pharmacokinetics of liposomal amphotericin B. When liposomal amphotericin B is freed from the liposomes, 90% of the drug is bound to proteins (albumin). Interactions on this level, certainly in malnourished patients with lower blood protein levels, can be expected when combined with other highly protein-bound drugs like efavirenz (99%), tenofovir (90%) or miltefosine (95-98%). Clinical as well as intrinsic metabolic effects of a change in bound/unbound drug fraction are unknown as well as the effect on tissue/intracellular distribution. Amphotericin B is not known to be a substrate, inducer or inhibitor of any of human multi-drug resistance transporters and no interactions are expected on this level with HAART medication or miltefosine.

### **Miltefosine**

In general, pharmacokinetics of miltefosine in HIV-positive patients are unknown and nothing is clinically known about drug-drug interactions between HAART and miltefosine. Miltefosine is metabolized, mainly, by phospholipase D and is not known to be a substrate for any of the cytochrome P450 enzymes (CYP450). Drug-drug interactions on the CYP450 level are thus not expected. Nevertheless, miltefosine can cause (severe) hepatotoxicity in a small selection of patients and might theoretically influence drugs which are mainly hepatically metabolized, like almost all PIs and NNRTIs. Miltefosine has been suggested *in vitro* as a substrate for the multi-drug-resistance transporter P-glycoprotein (P-gp), which is modulated intensively by e.g. ritonavir. Also lamivudine and efavirenz are known to be important substrates for P-gp and are both (relatively low) inducers of P-gp (~2-fold increase of activity *in vitro*). An increased activity of P-gp could lead to a reduced absorption of drug substrates from the gastrointestinal tract (lower plasma levels), but also decreased intracellular levels of drug substrates.

Similar to amphotericin B, interactions with HAART and amphotericin B on the level of protein-binding can be expected as well since miltefosine is 95-98% protein-bound. A small relative change in the fraction unbound to protein, would increase free levels of miltefosine dramatically and might have a high negative impact on the accumulation of miltefosine.

For miltefosine and antiretroviral drug levels, dried blood spots will be collected using Whatman 903 protein saver card. For Ambisome® levels, a 2 ml EDTA blood sample will be collected. These samples will be stored at -20 °C and shipped to the Slotervaart Hospital, Amsterdam where they will be analyzed by validated LC/MS/MS methodology.

The PK samples will be collected at Gondar site only. A minimum of 15 patients/arm will be included up to 30 patients/arm.

The specific PK timepoints are detailed in the two tables below according to each of the treatment arms:

## Schedule of pharmacokinetic events

### Arm 1: Monotherapy Ambisome® (40 mg/kg total dose)

| Activities                            | Matrix          | Volume per sample | Screening (day)
Day – 7 to Day 0 | Treatment (day)    |   |   |   |   |    |    |                    | Follow-up Period (months post treatment) |                 |                 |
|---------------------------------------|-----------------|-------------------|-------------------------------------|--------------------|---|---|---|---|----|----|--------------------|------------------------------------------|-----------------|-----------------|
|                                       |                 |                   |                                     | 1                  | 2 | 3 | 4 | 5 | 10 | 17 | 24                 | Day 58                                   | Day 210         | Day 390         |
| Rx - Ambisome® infusion               |                 |                   |                                     | X                  | X | X | X | X | X  | X  | X                  |                                          |                 |                 |
| PK AmphoB                             |                 |                   |                                     |                    |   |   |   |   |    |    |                    |                                          |                 |                 |
| PK AmphoB                 | EDTA plasma     | 2 mL blood        |                                     | X X X  |   |   |   |   |    |    | X X X  |                                          |                 |                 |
| Total volume blood taken for PK in mL |                 |                   |                                     | 10                 |   |   |   |   |    |    | 10                 |                                          |                 |                 |
| PK EFV/NVP/LPV/RTV                    |                 |                   |                                     |                    |   |   |   |   |    |    |                    |                                          |                 |                 |
| PK EFV/NVP/LPV/RTV        | DBS (duplicate) | ~50 µL blood      |                                     | X X  |   |   |   |   |    |    | XX     | XX                           | XX  | XX  |
| Total number of DBS (incl duplicates) |                 |                   |                                     | 4                  |   |   |   |   |    |    | 4                  | 4                                        | 4               | 4               |

- For a full curve: 2, 6 and 24h post-infusion (3 timepoints), 2mL of whole blood per sample for each timepoint → 500 µL plasma yields two duplicate samples of 250 µL → 50 µL will be used for total amphotericin B determination, 200 µL will be used for free amphotericin B determination (ultracentrifugation).
- Peak (toxicity) and trough (efficacy) levels for ARV drugs: steady-state concentration before taking dosage, peak levels for EFV/NVP/LPV/RTV approx. 4-5h after dose intake. EFV/NVP/LPV/RTV can be measured simultaneously in the same sample, since they have similar Tmax's.
- For PK of ARV's DBS's will be taken on the day of treatment initiation:
  - a) if patient is already on ARV's before study inclusion this will indeed be day 1
  - b) if ARV's will be initiated during study, DBS's for ARV PK will be sampled on the first day of ARV treatment, e.g. if ARV's are initiated on day 10, sampling will also be done on day 10.

In case of extended treatment, an additional sampling point will be taken **on the last AmBisome infusion, prior to dosing** for AmphoB & EFV/NVP/LPV/RTV.

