**Table 1: Current treatment options for patients with visceral leishmaniasis**

| Drugs                    | Limitations                                                                                                                                                                                                                |
|---------------------------------|-----------------------------------------------------------------------------------------------------------------------------------------------------------------------------------------------------------------------------------|
| Pentavalent antimonials  | toxicity (pancreatitis, hepatitis and cardiotoxicity: arrhythmias)
30 day iv/im treatment in hospital
painful injections                                                                                                    |
| Amphotericin B           | Needs slow IV infusion; infusion reactions (fever);
nephrotoxic; needs lab monitoring                                                                                                                                          |
| Liposomal amphotericin B | expensive
requires slow iv infusion over 1-2 hours
however long term hospitalization is not required                                                                                                                        |
| Miltefosine              | teratogenic
expensive
GI toxicity, hepato- & renal toxicity                                                                                                                                                                 |
| Paromomycin              | an aminoglycoside, therefore nephro- and ototoxicity possible: although reversible high tone audiometric shift may occasionally occur during treatment (Sundar, et al. 2007);
geographical variation in response (Hailu, 2010) |
| Pentamidine              | IM injection
Risk of developing diabetes mellitus                                                                                                                                                                              |

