#### On a sub-group of patients:

- Pharmacokinetics: Assessment of drugs level to monitor any drug-drug interaction between the proposed VL test drugs and concomitant antiretroviral drugs.
- Assessment of immune responses during treatment and follow-up by measurement of the cytokine profile (direct and by measuring specific mRNA in a microarray analysis) and by measuring immunoglobulins concentration.

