## 7.2. Doses and treatment regimens

### Dosing schedule:

#### AmBisome® monotherapy:

- Adapted from WHO recommendations for co-infected patients:  
40 mg/kg total dose: IV infusion of 5 mg/kg on day 1-5, 10, 17, 24.

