#### AmBisome® in combination with Miltefosine:

- AmBisome®: 30 mg/kg total dose: IV infusion 5 mg/kg on day 1, 3, 5, 7, 9, 11.
- Miltefosine: every day during 28 days.  
The dose is calculated according to the patient weight:
  - ≤ 25 Kg, the patient receives 50mg (i.e. 1 x 50mg capsule) per day.
  - > 25Kg, the patient receives 100mg (i.e. 2 x 50mg capsules) per day.

Miltefosine capsules should be taken with meals.

Dosages of 2 capsules per day should be divided into 2 individual doses to be taken in the morning and evening. In the event the patient vomits within 1 hour of a dose, that dose should be repeated. In the event of repeated vomiting the patient should be withdrawn from that treatment allocation and treated with rescue medication.

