| PK EFV/NVP/LPV/RTV / PK Miltefosine          |                 |                   |                                     |                    |   |   |   |   |                    |                              |                                        |                  |                  |
| PK EFV/NVP/LPV/RTV               | DBS (duplicate) | ~50 µL blood      |                                     | X X  |   |   |   |   |                    | X X              | X X                        | X X  | X X  |
| PK Miltefosine                               | DBS (duplicate) | ~50 µL blood      | X                                   |                    |   |   |   |   | X                  | X                | X                                      | X                |                  |
| Total number of DBS for PK (incl duplicates) |                 |                   | 2                                   | 4                  |   |   |   |   | 2                  | 6                            | 6                                      | 6                | 4                |

- For a full curve: 2, 6 and 24h post-infusion (3 timepoints), minimally 1.0 mL (preferably 2 mL in case of spilling etc.) of whole blood per sample for each timepoint → 500 µL plasma yields two duplicate samples of 250 µL → 50 µL will be used for total amphotericin B determination, 200 µL will be used for free amphotericin B determination (ultracentrifugation).
- Peak (toxicity) and trough (efficacy) levels for ARV drugs: steady-state concentration before taking dosage, peak levels for EFV/NVP/LPV/RTV approx. 4-5h after dose intake. EFV/NVP/LPV/RTV can be measured simultaneously in the same sample, since they have similar Tmax's.
- For PK of ARV's DBS's will be taken on the day of treatment initiation:
  - if patient is already on ARV's before study inclusion this will indeed be day 1
  - if ARV's will be initiated during study, DBS's for ARV PK will be sampled on the first day of ARV treatment, e.g. if ARV's are initiated on day 10, sampling will also be done on day 10.
- Blood drawn at day 29 for full blood count will also be used (no additional samples) to correlate Miltefosine level in DBS and plasma.

In case of extended treatment, an additional sampling point will be done **on the last AmBisome infusion, prior to dosing** for miltefosine, AmphoB and EFV/NVP/LPV/RTV.

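### In the monotherapy arm the day-1 amphotericin B sample at 24 h can fall during or at the end of the day-2 infusion, and nothing in the PK notes orders it before that infusion

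*Protocol*

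**What the plan says.** Section 8.6 refers the reader to two tables, one per arm, for the exact PK sampling times. The Arm 1 (monotherapy) table places three amphotericin B samples under day 1 and three under day 24. Its note reads "For a full curve: 2, 6 and 24h post-infusion (3 timepoints), 2mL of whole blood per sample for each timepoint". The Arm 2 (combination) table places three under day 1 and three under day 11, with the same times: "For a full curve: 2, 6 and 24h post-infusion (3 timepoints), minimally 1.0 mL".

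The infusion days differ between the arms (section 7.2). Monotherapy is "40 mg/kg total dose: IV infusion of 5 mg/kg on day 1-5, 10, 17, 24"; the combination is "30 mg/kg total dose: IV infusion 5 mg/kg on day 1, 3, 5, 7, 9, 11".

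The only infusion duration given is in Table 1 of the background, the general list of drugs and their limitations: "requires slow iv infusion over 1-2 hours". Sections 7.1 and 7.2 give no duration and no clock time for any infusion.

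A pre-dose instruction does appear in section 8.6, but only for the extra sample in extended treatment, which is taken "on the last AmBisome infusion, prior to dosing".

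**The concern.** In Arm 1 the day after the first PK day is itself an infusion day. In Arm 2 it is not. The same nominal sampling time can therefore mean different things in the two arms: a 24-hour level after one dose in Arm 2, and possibly a level that already contains the second dose in Arm 1.

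The third sample is the only one of the three that informs the later part of the day-1 curve. If it contains the second dose, the terminal slope and any exposure integrated to 24 h are wrong in one arm only. The error would be systematic, so enrolling 30 patients per arm rather than the minimum of 15 would not average it out.

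**Working it through.** **Inputs**

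- Sampling times: 2, 6 and 24 h post-infusion in both arms (section 8.6 notes). Start or end of infusion is not specified.
- Infusion days: Arm 1 on 1, 2, 3, 4, 5, 10, 17, 24; Arm 2 on 1, 3, 5, 7, 9, 11 (section 7.2 and the PK tables).
- Infusion duration D: 1-2 h (Table 1 only).
- Interval G from the start of the day-1 infusion to the start of the day-2 infusion: not stated. Assumed 24 h, examined from 22 to 26 h.

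**Check that the day-2 infusion is part of the regimen.** Arm 1: 8 infusions × 5 mg/kg = 40 mg/kg. Arm 2: 6 × 5 mg/kg = 30 mg/kg. Both stated totals are reproduced.

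**Time of the third sample, in hours from the start of the day-1 infusion**

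- Counted from the end of infusion: D + 24, which is 25 h (D = 1) or 26 h (D = 2).
- Counted from the start of infusion: 24 h.

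The day-2 infusion occupies G to G + D. With G = 24 h that is 24-25 h (D = 1) or 24-26 h (D = 2). Counted from the end, the sample falls exactly as the second infusion finishes. Counted from the start, it is due at the moment that infusion begins.

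**Arm 1, day 1: position of the third sample relative to the day-2 infusion**

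| G (h) | From end, D = 1 | From end, D = 2 | From start, D = 1 | From start, D = 2 |
|---|---|---|---|---|
| 22 | after it | after it | after it | at its end |
| 23 | after it | after it | at its end | during it |
| 24 | at its end | at its end | due as it starts | due as it starts |
| 25 | due as it starts | during it | before it | before it |
| 26 | before it | due as it starts | before it | before it |

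The sample is a clean first-dose level only if the anchor is the start of infusion and day 2 is not dosed early, or if the anchor is the end and day 2 is dosed at least 1-2 h later in the day. Where the two are due together, it is clean only if blood is drawn first.

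**The other PK days**

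- Arm 2, day 1: the next infusion starts at 48 h, so the margin is 48 − 26 = 22 h to 48 − 24 = 24 h.
- Arm 1 day 24 and Arm 2 day 11: these are the last infusions of the course, so there is no later dose to clash with.
- Arm 1, day 1, first two samples: 2-4 h and 6-8 h after the start, across both anchors. Both are clear of the second dose.

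**Size, as an illustration only.** Assume linear one-compartment kinetics and a mono-exponential half-life t (not in the documents). Let f = 2^(−24/t) be the fraction of the end-of-infusion level left 24 h later. The true first-dose level is proportional to f. A sample at the end of an identical second infusion is proportional to 1 + f. The ratio is (1 + f)/f.

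| Assumed t (h) | f | (1 + f)/f |
|---|---|---|
| 6 | 0.0625 | 17 |
| 8 | 0.125 | 9 |
| 12 | 0.25 | 5 |
| 24 | 0.5 | 3 |

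In this model the third reading (1 + f) is higher than the end-of-infusion peak (1), so it also exceeds the 2 h and 6 h readings. No declining terminal slope could be fitted to the three points.

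**The case against.** The strongest objection is that the clash is conditional. It needs the time to be counted from the end of infusion, the day-2 infusion to be given at about the same clock time, and the 1-2 h duration to apply. The protocol fixes none of these for the trial regimen. The table lists all three samples under day 1 and the note presents them as one complete curve, so a first-dose profile was evidently intended, and a careful site might draw the blood first. This stands: the finding is an unprotected sampling time, not a certain error. But the end-of-infusion reading is the ordinary one, same-time daily dosing is an ordinary practice, and the protocol writes a pre-dose rule for one PK sample and not for this one.

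A reader might infer that the monotherapy first-dose curve cannot be compared with the combination arm, or that accumulation by day 24 would be hidden. The documents do not support that. The 2 h and 6 h samples remain comparable, and a model fitted to recorded dose and sampling times could still use the third. Nor does the protocol specify either comparison. The stated sub-group aim is "Assessment of drugs level to monitor any drug-drug interaction between the proposed VL test drugs and concomitant antiretroviral drugs". The synopsis does list the kinetics of AmBisome and miltefosine among the other objectives, and section 8.6 expects a protein-binding interaction between amphotericin B and miltefosine, so a between-arm look is plausible. Day 1 is a weak place for it, though, because miltefosine starts that same day.

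The fold figures are also open to challenge. The half-lives are assumed, and section 8.6 itself describes the kinetics of the liposomal drug as non-linear and highly variable. That stands, and the figures should be read only as showing that contamination would not be trivial.

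**Conclusion.** The point holds in a limited form. In Arm 1, the third day-1 amphotericin B sample can fall during or at the end of the day-2 infusion, and nothing in the PK note prevents it. With the time counted from the end of a 1-2 h infusion and same-time dosing, it is drawn 25-26 h after the first infusion began, exactly as the second ends. A different anchor, or a day-2 infusion 1-2 h later, would avoid this.

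One point of three is at risk, in one arm and on one of its two PK days, together with any terminal slope or 24-hour exposure built on it. The size is not determined by the documents; the 3- to 17-fold range rests on assumed half-lives of 24 to 6 h and linear kinetics.

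A reader might also infer that the trial's conclusions are affected. They are not. This is a sub-study at one site with 15 to 30 patients per arm, reported separately (section 10.8), with no bearing on the day-29 endpoint or the stopping boundaries. It is worth correcting because literal compliance under regular daily dosing contaminates the sample and the remedy is almost free.

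**What to change.** Amend the amphotericin B note in both PK tables of section 8.6:

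1. Define one anchor, start or end of infusion, for all three samples, so that a single curve does not mix time origins.
2. State that the third Arm 1 day-1 sample is taken immediately before the day-2 infusion starts.
3. Use the same nominal time in Arm 2 and on the last infusion day of each arm. With same-time daily dosing this is about 24 h from the start of infusion. If the end is chosen as the anchor, it is 24 − 2 = 22 h to 24 − 1 = 23 h after the end, and the label should say so.
4. Record actual infusion start, stop and sampling times, and use them in the analysis.

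The cost is a sentence or two in each note and the recording of clock times. No sample, blood volume or visit is added, and the infusion schedule does not change.

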**Arm 2: Combination therapy Ambisome® (30 mg/kg total dose) + 28 days of miltefosine**

| Activities                                   | Matrix          | Volume per sample | Screening (day)
Day – 7 to Day 0 | Treatment (day)    |   |   |   |   |                    | End of Treatment (day)
29 | Follow-up Period (days post treatment) |                  |                  |
|----------------------------------------------|-----------------|-------------------|-------------------------------------|--------------------|---|---|---|---|--------------------|------------------------------|----------------------------------------|------------------|------------------|
|                                              |                 |                   |                                     | 1                  | 3 | 5 | 7 | 9 | 11                 |                              | Days 58                                | Days 210         | Days 390         |
| Rx - Ambisome ® infusion          |                 |                   |                                     | X                  | X | X | X | X | X                  |                              |                                        |                  |                  |
| Rx – Miltefosine                             |                 |                   |                                     | Start              |   |   |   |   |                    | End                          |                                        |                  |                  |
| PK AmphoB                                    |                 |                   |                                     |                    |   |   |   |   |                    |                              |                                        |                  |                  |
| PK AmphoB                        | EDTA plasma     | 2 mL blood        |                                     | X X X  |   |   |   |   | X X X  |                              |                                        |                  |                  |
| Total volume blood taken for PK in mL        |                 |                   |                                     | 10                 |   |   |   |   | 10                 |                              |                                        |                  |                  |
| PK EFV/NVP/LPV/RTV / PK Miltefosine          |                 |                   |                                     |                    |   |   |   |   |                    |                              |                                        |                  |                  |
| PK EFV/NVP/LPV/RTV               | DBS (duplicate) | ~50 µL blood      |                                     | X X  |   |   |   |   |                    | X X              | X X                        | X X  | X X  |
| PK Miltefosine                               | DBS (duplicate) | ~50 µL blood      | X                                   |                    |   |   |   |   | X                  | X                | X                                      | X                |                  |
| Total number of DBS for PK (incl duplicates) |                 |                   | 2                                   | 4                  |   |   |   |   | 2                  | 6                            | 6                                      | 6                | 4                |

- For a full curve: 2, 6 and 24h post-infusion (3 timepoints), minimally 1.0 mL (preferably 2 mL in case of spilling etc.) of whole blood per sample for each timepoint → 500 µL plasma yields two duplicate samples of 250 µL → 50 µL will be used for total amphotericin B determination, 200 µL will be used for free amphotericin B determination (ultracentrifugation).
- Peak (toxicity) and trough (efficacy) levels for ARV drugs: steady-state concentration before taking dosage, peak levels for EFV/NVP/LPV/RTV approx. 4-5h after dose intake. EFV/NVP/LPV/RTV can be measured simultaneously in the same sample, since they have similar Tmax's.
- For PK of ARV's DBS's will be taken on the day of treatment initiation:
  - if patient is already on ARV's before study inclusion this will indeed be day 1
  - if ARV's will be initiated during study, DBS's for ARV PK will be sampled on the first day of ARV treatment, e.g. if ARV's are initiated on day 10, sampling will also be done on day 10.
- Blood drawn at day 29 for full blood count will also be used (no additional samples) to correlate Miltefosine level in DBS and plasma.

In case of extended treatment, an additional sampling point will be done **on the last AmBisome infusion, prior to dosing** for miltefosine, AmphoB and EFV/NVP/LPV/RTV.

